**Fig. 1 Fig1:**
[figure not shown]
Flow diagram including the process of enrollment, allocation, interventions, and assessments

### Ethics approval

The study will be conducted in accordance with the Declaration of Helsinki and has been approved by the Ethics Committee of the FAU’s Medical Faculty (protocol number 10_21 B). Protocol amendments will be communicated in writing to the Ethics Committee, as well as to other relevant parties, including the German Research Foundation (DFG) and the German Clinical Trials Register (DRKS).

### Power analysis

An a priori power analysis has been conducted using G*Power (version 3.1.9.6) for sample size estimation, based on the findings of a preliminary study [20]. The analysis is limited to the reference biomarkers cortisol and sAA, as no available data provide insights into the modifiability of inflammatory response patterns.

As demonstrated in the aforementioned preliminary study [20], the findings suggest a high modifiability of cortisol and sAA responses through the manipulation of psychological coping mechanisms. Specifically, a large effect was observed in the difference in cortisol response habituation between intervention and control group (*d* = 0.81), while a moderate-to-large effect was found for the difference in sAA response habituation (*d* = 0.67). Based on these findings, medium-to-large effects are expected for differences between experimental groups with regard to their difference in habituation of biological stress system activity. Power analyses revealed a sample size of *N* = 111 (*n* = 37), using an effect size of *f*^2^ = 0.30, *α* = 0.05, 1-*β* = 0.80, number of groups = 3. To address the anticipated 10% dropout rate caused by non-appearance of participants on study day 2 or insufficient biological sample volumes, an additional nine participants (three per condition) will be recruited and tested in this study, resulting in a total sample size of *N* = 120.

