## Methods

### Study design

The study is designed as a randomized controlled, single-center, and single-blinded trial, in which participants will be randomly assigned to one of two intervention groups (rumination vs. self-compassion) or a control condition (see “Randomization”) with an allocation ratio of 1:1:1. The study employs a superiority trial design, aiming to determine whether one of the two cognitive coping interventions is more effective in modifying the responsiveness and habituation of biological stress systems compared to the control condition. The design encompasses repeated measurements of each group, i.e., each group will undergo two experimental sessions (t1 and t2) comprising stress test exposures, and within each experimental session, repeated biological and psychological outcome assessments will take place (see Table 1).

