### Data preparation and statistical analysis

Data preparation and statistical analysis will be performed using IBM SPSS Statistics 26 (IBM Corp., Armonk, NY, USA). Following our pre-registered analysis plan [60], data will be screened for outliers using *z*-scores, and outliers which differ more than 3 standard deviations from the participants’ mean will be excluded from further analysis. In addition, participants will be excluded in case of elevated cortisol levels (e.g., > 12 nmol/L or *z* > 3.29) after arrival at the laboratory (i.e., at baseline) and after accommodating to the testing situation (i.e., at − 1 min relative to the TSST). Additionally, non-adherent participants whose missing values exceed 25% of the data will also be excluded from the analysis. In the next step, Kolmogorov–Smirnov tests will be conducted in order to check for normal distribution. If necessary, data will be log-, ln-, or inverse transformed to reduce skewness of biological data.

To analyze the data (i.e., to compare self-report measures as well as biological response and habituation indices between experimental groups), we will use separate analyses of covariance (ANCOVAs). Sex and BMI will be used as covariates in analyses of biological data, as these two variables have been repeatedly shown to be highly relevant for stress system activity [61, 62]. We will use the standard *p* < 0.05 criteria for determining if the ANCOVA and the post hoc test suggest that the results are significantly different from those expected if the null hypothesis were correct. The post-hoc Bonferroni test adjusts for multiple comparisons.

To investigate associations between primary psychological outcome measures and indices of biological stress measures, we will compute separate hierarchical linear regression models, regressing biological outcome measures onto psychological outcome variables. Again, sex and BMI will be included as covariates in these analyses. When examining state variables, the respective trait variable will be included as covariate in regression analyses.

We expect that certain psychological (e.g., emotion regulation, coping), demographic (e.g., age, gender, sex), and anthropometric (e.g., BMI) variables may be related to biological stress system activity. Therefore, we will test for relationships between these variables and primary outcome measures of biological stress responses in an exploratory fashion.

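### The power statement prints f² = 0.30 where N = 111 requires f = 0.30, and its nine extra participants do not cover the stated 10% dropout

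*Protocol article*

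**What the plan says.** The Power analysis section gives the result as "Power analyses revealed a sample size of *N* = 111 (*n* = 37" per group), "using an effect size of *f*^2^ = 0.30", with alpha 0.05, power 0.80 and "number of groups = 3". It cites preliminary intervention-versus-control effects on habituation of d = 0.81 for cortisol and d = 0.67 for salivary alpha-amylase (sAA).

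On attrition it continues: "To address the anticipated 10% dropout rate", due to missed second sessions or too little sample material, "an additional nine participants (three per condition) will be recruited and tested in this study", "resulting in a total sample size of *N* = 120".

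Three other places bear on how the power figure is read:

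- Study design states a superiority trial "aiming to determine whether one of the two cognitive coping interventions is more effective" than the control condition.
- Hypothesis 8 puts habituation lowest under rumination and strongest under self-compassion, so control lies between them.
- Data preparation and statistical analysis plans ANCOVAs, with sex and BMI as covariates for biological data, followed by post-hoc tests: "The post-hoc Bonferroni test adjusts for multiple comparisons". The same section excludes outliers beyond 3 SD, participants with elevated cortisol before the stressor, and those with more than 25% missing data.

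**The concern.** A sample-size statement should let a reader recover N from its inputs. This one does not. The printed effect size and the printed N cannot both be right for a three-group test, and the dropout allowance does not match the dropout rate in the same sentence.

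An f² of 0.30 is more than three times the 0.09 that the study was evidently sized for. Anyone checking the calculation, or reusing it for a later trial, would take the assumed effect to be far larger than it was. On dropout, if attrition runs as the authors expect, the trial ends slightly below the power it reports.

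There is also a point of interpretation. The section does not say which test the 80% belongs to. A reader could carry it over to the comparisons with control and take a non-significant one as a negative result from a trial with 80% power for that comparison.

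**Working it through.** **Inputs.** From Power analysis: 3 groups, alpha 0.05, power 0.80, f² = 0.30 as printed, N = 111, dropout 10%, nine extra, 120 in total, d = 0.81 and 0.67. From Study design: 1:1:1 allocation. From the analysis section: two covariates and Bonferroni post-hoc tests.

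**1. Reproducing N = 111.** For the omnibus F-test, the non-centrality is λ = N·f², with df1 = 2 and df2 = N − 3 − (number of covariates).

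| Effect size | Smallest N for 80% | λ at that N | Power at that N |
|---|---|---|---|
| f = 0.30 (f² = 0.09) | 111 | 111 × 0.09 = 9.99 | 0.803 |
| f² = 0.30 (f = √0.30 = 0.548) | 36 | 36 × 0.30 = 10.8 | 0.81 |

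Both values of N are the same with zero, one or two covariates. At f² = 0.30, 111 participants would give power above 0.999.

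Other routes from f² = 0.30 do not reach 111 either:

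- one numerator degree of freedom needs 29;
- alpha divided by 2 to 100 tests needs 43 to 80;
- a regression test needs 29 to 87 for 1 to 20 predictors, and 106 with 30 predictors, a model the protocol does not describe.

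The stated N reproduces exactly once f² is read as f.

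**2. Dropout.**

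- 9/120 = 7.5% (9/111 = 8.1%).
- 120 × 0.90 = 108, or 36 per arm, three short of 111.
- To retain 111 after 10% loss: 111/0.9 = 123.3, so 124, or 126 in equal arms (37/0.9 = 41.1, so 42 per arm). Even the looser 111 × 1.1 = 122.1 exceeds 120.

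Omnibus power at f = 0.30:

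| Analysed N | Power |
|---|---|
| 120 | 0.836 |
| 111 | 0.803 |
| 108 | 0.79 |
| 102 | 0.766 |
| 99 | 0.752 |

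The last two rows rest on an assumption: a further 5% of 120 (6 people, leaving 102) or about 8% (9 people, leaving 99) lost to the analysis exclusions. The protocol gives no exclusion rate.

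**3. What the omnibus figure means for pairs of arms.** The pairwise non-centrality is d·√(n/2), with the error df pooled over the three arms. Assumptions: n = 36 per arm, three Bonferroni comparisons (alpha 0.05/3 each), and no precision gained from covariates.

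- *Evenly spaced means* (−Δ, 0, +Δ): f = Δ·√(2/3), so Δ = 0.30 × √1.5 = 0.367 against control, and 2Δ = 0.735 between the extreme arms.
- *One arm alone differs*: f = d·√2/3, so d = 0.30 × 3/√2 = 0.636.

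| Comparison | d | Bonferroni power |
|---|---|---|
| Either arm vs control, evenly spaced | 0.367 | 0.20 |
| Self-compassion vs rumination, evenly spaced | 0.735 | 0.75 |
| One arm alone differs, vs control | 0.636 | 0.61 |
| Preliminary sAA effect vs control | 0.67 | 0.66 |
| Preliminary cortisol effect vs control | 0.81 | 0.84 |

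The number of comparisons is not stated. With two instead of three, the evenly spaced comparison with control has 0.24, d = 0.67 has 0.71 and d = 0.81 has 0.88.

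**The case against.** The strongest reply is that little depends on this. The trial was evidently sized at f = 0.30, so the error is one superscript, and no sample size, test or decision changes. The dropout shortfall costs about one percentage point. The calculation also takes no credit for sex and BMI: if they explained 5% of residual variance (an assumption; the protocol gives no figure), power at 108 would be back to about 0.81. All of this stands, and it is why the point is minor. It does not make the printed effect size or the dropout allowance correct.

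A reader might go further and infer that the 80% is false for the trial's aim, or that the trial has only 20% power against control. The protocol does not support either reading. The Power analysis section lists only the inputs of a three-group test and never assigns the 80% to comparisons with control. Sizing the omnibus test is consistent with an ANCOVA followed by post-hoc tests. The 20% needs evenly spaced means, whereas Hypothesis 8 gives only an order. If one arm alone differs, power is about 60%, and at the preliminary cortisol effect it is 84%. The hypotheses also cover self-compassion against rumination, not only control. The pre-registered analysis plan, which is not shown, may define the contrasts.

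A reader might also take 75–77% as the power after the planned exclusions. That cannot be derived from the protocol. No exclusion rate is given, and exclusion for more than 25% missing data may overlap with the missed sessions and low sample volumes already in the 10%.

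**Conclusion.** Two statements in the Power analysis section are wrong as written. The effect size should read f = 0.30 (f² = 0.09); the printed f² = 0.30 implies N = 36, not 111. N = 111 itself is right. Nine extra participants cover 7.5% of 120, and the stated 10% dropout leaves 108, with omnibus power of about 79% instead of 80%.

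The outlier, cortisol and missing-data exclusions are outside the allowance and could lower power further. The size of that loss is unknown; 75–77% is an illustration under an assumed further 5–8% of 120 excluded.

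That the power figure belongs to the omnibus test is a matter for clarification, not an error. Pairwise power against control at f = 0.30 runs from about 20% to about 60% over the two patterns of means examined, under the assumptions listed above.

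Severity: a minor correction. Nothing here shows that 120 is the wrong number to recruit.

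**What to change.** In the Power analysis section:

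1. Replace the effect size by f = 0.30 (f² = 0.09).
2. Keep N = 120. State that a 10% dropout leaves 108 expected analysed (36 per arm), with about 79% power for the three-group omnibus test. Note that the analysis exclusions are not in this allowance. Give a figure for them only with an exclusion rate labelled as an assumption.
3. As a clarification, say that the 80% was computed for the omnibus test, and give Bonferroni pairwise power as a range with its assumptions (three comparisons, 36 per arm, no covariate gain). At f = 0.30, power against control is about 20% if means are evenly spaced and about 60% if one arm alone differs; self-compassion against rumination has 75% if evenly spaced. At the preliminary effects against control it is 66% (d = 0.67) and 84% (d = 0.81).

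The cost is a few sentences and a slightly less favourable stated power. Recruitment, allocation and the planned tests stay as they are.

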### Status and timeline of the study

Recruitment of participants will start in August 2024. Data collection will commence in September 2024 and continue until September 2026. Data analysis will be conducted upon completion of the entire data collection. No preliminary data analyses will be performed.

### Experimental conditions

Figure 1 provides an overview of the allocation of participants into three experimental conditions. Participants assigned to intervention group 1 will take part in a rumination intervention, whereas participants from intervention group 2 will take part in a self-compassion intervention. Condition 3 will serve as an active control group in which participants are instructed to think neutrally about a specified topic and record their thoughts in written form.

### Tasks and interventions

#### Intervention group 1: rumination

According to the Response Styles Theory [21], rumination is described as repetitive thought process focused on the causes, consequences, and symptoms of negative affect, which may generally cause maintenance and amplification of depressive symptoms. Furthermore, Clark and Wells [22] describe rumination that specifically occurs after psychosocially stressful events (post-event rumination) as persistent processing or reflection about a previous social interaction.

As has been revealed by previous research, rumination is generally associated with indicators of lower psychological well-being, as it predicts the occurrence of future depressive episodes [23]. Additionally, individuals who strongly ruminate about prior stressful events exhibit dysfunctional biological adaptation mechanisms, including higher cortisol responses to acute stress [24], and sustained activation of the HPA axis and the inflammatory system [25]. Preliminary work has also revealed associations between stressor-related rumination and increased stress-induced responses of HPA axis activity to repeated acute stress, suggesting that rumination may impair the habituation of biological stress system activity [14]. Due to the persistent and passive focus on negative emotions in stressful situations as well as the impaired ability to adequately biologically adapt to acute and repeated stress, rumination is thus considered to have detrimental effects on long-term health.

As demonstrated by multiple studies, rumination can be experimentally induced, which affects the activation of the HPA axis and the inflammatory system [25, 26]. An analysis with preliminary data reveals that stressor-related rumination can be induced by a short-term writing intervention which leads to a reduction of HPA axis habituation [20]. Analogous to this experimental approach, the planned study aims to manipulate rumination as coping mechanism to gain insight into whether it may lead to maladaptive biological adaptation. To this end, the first intervention is designed to experimentally induce rumination by instructing participants to ruminate about their first stress exposure and, in particular, about their negative feelings and to write down their thoughts.

#### Intervention group 2: Self-compassion

Self-compassion refers to a personality trait that describes an open and caring attitude towards oneself in the face of failure and perceived shortcomings. It is characterized by self-kindness, a perception of common humanity and mindfulness in dealing with negative thoughts and emotions [27–29]. Overall, research indicates that individuals reporting higher self-compassion are mentally and physically healthier [30]. Our own preliminary work has shown that individuals with higher self-compassion exhibit lower cortisol and salivary alpha-amylase (sAA) responses and thus healthier biological adaptation to acute stress [13]. Due to the increased stress resilience (i.e., the improved ability to experience negative emotions during stress, and to show adaptive biological stress responses), self-compassion is thus considered being protective with regard to long-term health.

As initially demonstrated by Neff and Germer [31], self-compassion can be enhanced through intervention. Thus, the Mindful Self Compassion program developed by Neff and Germer [31] demonstrably leads to a sustained increase in self-compassion and mindfulness and to a reduction in anxiety and depression. It has also been shown that the program leads to increases in overall well-being [32] and keeps blood glucose levels stable in diabetic patients [33]. Similarly, Diedrich et al. [34] presented a training designed to enhance self-compassion, which has been shown to reduce depressive mood in patients with major depressive disorder, making it an effective short-term intervention, at least on a psychological level. Due to its high efficiency, the procedure described by Diedrich et al. [34] will be applied in the present study in order to manipulate self-compassion. Therefore, participants from intervention group 2 will be instructed to think about their first stress exposure, to actively engage in self-compassion, and to write down their thoughts.

#### Control group

To ensure that any changes in stress responses are attributed to the effect of specific cognitive strategies (rumination vs. self-compassion), rather than to engaging in a thinking and writing task per se, a control group will be included in which participants will be instructed to think neutrally about a specified topic (e.g., a description of everyday life) and to write down their thoughts.

### Assessment of sample characteristics during screening

Demographic (e.g., age, gender, sex), socioeconomic (e.g., occupation), anthropometric (e.g., BMI), health-related (diseases, medication intake), and biobehavioral (e.g., smoking status) variables will be electronically assessed during screening and will partly be used to determine eligibility for participation (see “Participants”).

### Psychological assessments during screening

During the screening process, additional psychological variables (e.g., self-reported social anxiety) will be electronically assessed, which will partly be used to determine eligibility for participation (see “Participants”).

#### Self-reported social anxiety

To exclude altered response patterns of HPA axis activity in social anxiety disorders [35], the severity of symptoms will be assessed using the Social Phobia Scale [SPS, 36] and the Social Interaction Anxiety Scale [SIAS, 36]. Each scale comprises 20 items designed to identify situations where socially anxious individuals typically experience emotions of fear. The SPS assesses anxiety in performance situations (e.g., “I get tense when I speak in front of other people”), while the SIAS assesses anxiety in social interaction situations (e.g., “I have difficulty making eye contact with others.”). Three negatively phrased items of the SIAS will be reverse-coded, and total scores will be calculated by summing up items on each scale. The presence of a social anxiety disorder will be determined by comparing the scale scores to predefined cutoff values (SPS > 21, SIAS > 32).

#### Self-reported depressiveness

To exclude altered cortisol response patterns in depressive disorders [37], the severity of depressive symptoms will be assessed using a German version of the Center for Epidemiological Studies Depression Scale [CES-D, 38] termed “Allgemeine Depressionsskala Langform” (ADS-L) from Hautzinger et al. [39]. The 20-item scale determines the severity of depressive symptoms, by asking participants how often in the past week they experienced symptoms such as “I felt sad” or “My appetite was poor”. Four items will be reverse-coded, and total scores will be calculated by summing up all item scores. The presence of a depressive disorder will be determined by comparing the scale scores to a predefined cutoff value (> 22).

#### Perceived stress

To assess participants’ perceived stress, a German version of the 10-item Perceived Stress Scale [PSS, 40] from Klein et al. [41] will be used. In this questionnaire, participants will be asked to indicate how often they have experienced stress in the past month, for example, “In the last month, how often have you felt nervous and ‘stressed’?”. Ratings will be made on a 5-point Likert scale ranging from “never “ to “very often “. After reverse-coding four items, overall sum scores will be computed.

#### Rumination

Trait rumination will be assessed using a German version of the Response Style Questionnaire [RSQ, 42] from Kühner, Huffziger, and Nolen-Hoeksema [43]. The scale evaluates how participants typically respond to depressive mood and includes two subscales Rumination (21 items) and Distraction (11 items). Items on the Rumination scale depict reactions focusing on depressive mood, its causes, and consequences (e.g., “Think about how alone you feel”), while items on the Distraction scale describe active and problem-solving approaches to reduce feelings of depression (e.g., “Help someone else with something in order to distract yourself”). Ratings will be recorded on a 4-point Likert scale ranging from “almost never” to “almost always,” with nine negative items being reverse-coded. Subsequently, scores will be computed by summing up all items for each response style.

#### Self-compassion

To assess trait self-compassion, a German version of the Self Compassion Scale [SCS, 28] from Hupfeld and Ruffieux [SCS-D, 27] will be utilized. The scale comprises 12 items addressing self-kindness (e.g., “I try to be loving towards myself when I’m feeling emotional pain.”), self-judgment (e.g., “I’m disapproving and judgmental about my own flaws and inadequacies.”), perceptions of common humanity (e.g., “When things are going badly for me, I see the difficulties as part of life that everyone goes through.”), perceptions of isolation (e.g., “When I think about my inadequacies, it tends to make me feel more separate and cut off from the rest of the world.”), mindfulness (e.g., “When something upsets me I try to keep my emotions in balance.”), and over-identification (e.g., “When I’m feeling down, I tend to obsess and fixate on everything that’s wrong.”). Ratings will be made on a 5-point Likert scale ranging from “almost never” to “almost always”. Following reverse-coding of items assessing perceptions of self-judgment, isolation, and over-identification, total sum scores will be computed.

